### Sample size

We used the method described by Donner [42] to calculate the sample size, based on calculation of odds ratios. The smallest difference between the intervention and control groups that we want to be able to detect in the proportion of respondents with a passing score is 10 percentage points. Assuming that 10% of the control group will achieve a passing score (a conservative estimate, based on data from the pilot [32], power of 0.90, a two-sided *P* value of 0.05, we estimate that 397 participants will be needed to be able to detect an improvement of 10% in the intervention group. Studies of the effects of drug fact boxes and a primer to help people understand risk suggest that this is likely to be an adequate sample size [25, 26]. Allowing for a 20% loss to follow-up gives us a sample size of 497 participants. More specific information about the trial and this protocol is summarised in the SPIRIT checklist (Additional file 5).

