### Random allocation

#### Methods for stratification and randomisation

We will stratify our sample proportionately by the highest level of education attained (primary school and below, secondary school, or tertiary education) and whether their children are in a school that is in the intervention or control arm of the IHC primary school resources trial.

We will use computer-generated blocked randomisation. A statistician or other senior researcher at the clinical trials unit at the College of Health Sciences, Makerere University who is not a member of the IHC research team will generate the allocation sequences for the two comparison groups. A web-based random number generator at www.sealedenvelope.com will be used to obtain random permuted blocks with varying block sizes of 4 and 6, and equal allocation ratios, both within blocks and within strata, as shown in Table 1 below.

**Table 1 Tab1:** Excerpt from a sample randomisation list^a^

Column 1	2	3	4	5	6	7
Block identifier	Block size	Sequence within block	Allocation group	Education stratum	Number within stratum	Study code
1	4	1	Group A	≤ primary	1	YL9
1	4	2	Group A	≤ primary	2	PX5
1	4	3	Group B	≤ primary	3	JP3
1	4	4	Group B	≤ primary	4	OB2
2	4	1	Group A	≤ primary	5	XD6
2	4	2	Group A	≤ primary	6	JD0
2	4	3	Group B	≤ primary	7	NU5
2	4	4	Group B	≤ primary	8	SS0
3	4	1	Group B	≤ primary	9	SK0
3	4	2	Group A	≤ primary	10	QN4

^a^List generated from www.sealedenvelope.com

As shown in Table 1 above, the list will have study codes that are unique for each participant (column 7), against which we will attach an ordered array of numbers (column 6) spanning the full breadth of our sample size within each stratum. Each study code will be printed on a separate opaque envelope.

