After removing some questions, we modified the remaining questions that did not perform well according to the Rasch analysis, and revised and simplified the text where needed. The items were also translated into Luganda and adapted for audio administration. In the second psychometric testing, the Claim Evaluation Tools were administrated to a similar sample as described in the first psychometric test, but approximately half of the sample received the items as a written questionnaire in English and the other half received the Luganda audio versions. The results of this test suggested that the items administered in English performed very well according to the Rasch model, and with high reliability. Furthermore, the items were also less difficult than what was found in the first psychometric testing before the revisions. The results also suggested that the Luganda versions of items had evidence of under-discrimination and differential item functioning in seven out of 29 items. These items were revised to improve fit to the Rasch model.

Based on these two psychometric tests, a selection of 18 multiple-choice items addressing the nine concepts that the IHC podcast covers will be used (Additional file 3). Each key concept is evaluated by two items. We chose items with high reliability (fit to the Rasch model) and those with an appropriate difficulty level.

Parents in both arms of the trial will complete the questionnaires after they have listened to the podcast or public service announcements. Research assistants will deliver the questionnaires, ensuring that the parents have adequate time to answer the questions and ensure that the questionnaires have been completed fully.

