#### Subgroup and exploratory analyses

Education might affect people’s ability to understand and apply the concepts and to answer questions in the Claim Evaluation Tools. We will explore whether there are differences in the effects of the intervention for participants with primary school education versus secondary school education versus tertiary education. We will conduct tests for interaction for the primary outcomes, and we will use published guidelines to interpret the results of these subgroup analyses [41], using the models described above.

The children of all participants will be participating in a parallel trial evaluating the effects of IHC teaching resources, designed to teach P.5 school children concepts that they need to understand and apply to assess treatment claims [34], but only half of them will be receiving the IHC teaching resources. By testing for interaction between IHC teaching resources and the podcast in the statistical models described above we will evaluate whether the combination of the podcast and the IHC teaching resources improves outcomes among parents, compared to the podcast alone.

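### The 10% control pass rate is called conservative without support, and 397 evaluable participants give about 80% power at that rate, not the stated 90%

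*Protocol article*

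**What the plan says.** All the inputs but one are in the Sample size section of the protocol article.

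- **Target:** the smallest difference to be detected "in the proportion of respondents with a passing score is 10 percentage points".
- **Control rate:** "Assuming that 10% of the control group will achieve a passing score (a conservative estimate, based on data from the pilot". The pilot rate itself is not given, and no range of control rates is shown.
- **Error rates:** the stated power is 0.90, with a two-sided test at the 5% level.
- **Resulting size:** the section concludes, after its significance level, "value of 0.05, we estimate that 397 participants will be needed to be able to detect an improvement of 10% in the intervention group".
- **Method:** "We used the method described by Donner [42] to calculate the sample size, based on calculation of odds ratios".
- **Loss to follow-up:** 20%, which takes 397 to 497.
- **Allocation** (Methods for stratification and randomisation): "equal allocation ratios, both within blocks and within strata".

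Two other statements bear on the control rate. Outcome assessment reports that, at the second psychometric test, "the items were also less difficult than what was found in the first psychometric testing before the revisions". Subgroup and exploratory analyses says of the participants' children that "only half of them will be receiving the IHC teaching resources".

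**The concern.** Calling a planning value conservative tells the reader that an error in it is more likely to help the trial than to hurt it. For a fixed absolute difference, that depends on which side of 10% the true control rate lies. The binomial variance grows as the rate moves from 10% towards the middle of the scale, so a control rate of 20% or 30% needs a larger trial to detect the same 10 points. If the revised items are easier, or if some control parents learn from their children's lessons, the error would lie on the side where power is lost.

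The pass rate is one of two primary outcomes. If power is believed to be 90% and protected, a non-significant pass-rate result may be read as evidence against a 10-point effect when the trial had a substantial chance of missing one. The stated power at 10% therefore has to be checked first, because every sensitivity figure starts from it.

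**Working it through.** **Inputs.** From the document: control rate p1 = 0.10, difference 0.10 (so p2 = 0.20), two-sided alpha 0.05, power 0.90, 1:1 allocation, 20% loss. Control rates other than 10% are my assumptions, shown as a range.

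**Step 1: the plan's own figure.** With pooled variance under the null, p̄ = (p1 + p2)/2, and the number per arm is

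n = [z(0.975)·√(2p̄(1−p̄)) + z(power)·√(p1(1−p1) + p2(1−p2))]² / (p2−p1)².

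Here p̄ = 0.15, √(2 × 0.15 × 0.85) = 0.505 and √(0.09 + 0.16) = 0.500.

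- At 90% power: (1.960 × 0.505 + 1.282 × 0.500)² / 0.01 = 265.9, so 266 per arm and **532 in total**.
- At 80% power: (1.960 × 0.505 + 0.842 × 0.500)² / 0.01 = 199.0, so 199 per arm and **398 in total**.

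Other formulas at 90% power give these totals: unpooled 526, pooled variance under both hypotheses 536, log odds ratio 556, arcsine 522, continuity-corrected 572. A one-sided test gives 434. None is close to 397. At 80% power the pooled and unpooled formulas give 398 and 394. So 397 is not reproduced at the stated 0.90, but it agrees closely with 0.80.

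The allowance for loss does reproduce: 397/0.80 = 496.25, rounded up to 497.

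**Step 2: power of 397 at the plan's own rate.** With 198.5 per arm,

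z = [0.10 × √198.5 − 1.960 × 0.505] / 0.500 = (1.409 − 0.990)/0.500 = 0.838,

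so power is Φ(0.838) = 0.80.

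**Step 3: other control rates, difference held at 10 points.** The same two formulas give:

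| Control rate | Total evaluable for 90% power | Power with 397 evaluable |
|---|---|---|
| 5% | 376 | 0.92 |
| 10% | 532 | 0.80 |
| 15% | 670 | 0.70 |
| 20% | 784 | 0.63 |
| 30% | 954 | 0.55 |
| 45% | 1048 (maximum) | 0.51 |
| 80% | 532 | 0.80 |

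The curve is symmetric about 45%, so 80% gives the same result as 10%, and rates above 80% need fewer participants again.

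**Step 4: does the sensitivity remain without losses, or with the size that gives 90%?** If all 497 were analysed, power would be 0.88 at a 10% control rate, 0.73 at 20% and 0.65 at 30%. With 532 analysed it would be 0.90, 0.76 and 0.68. The fall with rising control rate is therefore separate from the mismatch between 397 and 0.90.

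**The case against.** The strongest reply is that the pilot rate cannot be seen. If it was below 10%, rounding up to 10% was cautious on this very scale: 5% needs 376 and 10% needs 532. The pass mark of 11 out of 18 was set for the version of the tool to be used, so the 10% may already allow for easier items. This stands, and it is why the label cannot be called false.

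A reader might infer from the easier items and the children's lessons that the control rate must exceed 10%. The document does not support that. The remark about difficulty directly follows one about items administered in English. Seven of the 29 Luganda items showed under-discrimination or differential item functioning and were revised, and the final 18 were then selected. No pass rate follows from any of this. Spillover from child to parent is something the protocol will explore by an interaction test; it predicts no size for it. Both points are suggestive only.

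A reader might also infer that 10% is the most favourable value possible, or that every higher rate lowers power. Neither is so: 5% gives more power, 80% gives the same, and rates above 80% give more.

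The odds-ratio basis gives the word a coherent meaning. At a fixed odds ratio of 2.25 (0.25/0.111), a low control rate is the demanding case, with 964 needed at 5%, 532 at 10% and 328 at 20%. But no odds ratio is stated as the target; the section states 10 percentage points. This reply also leaves Step 1 untouched, since the log odds ratio formula needs 556 at 90% power.

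Finally, the analysis section already promises a confidence interval for the difference, which limits over-reading of a null result, and the calculation does not concern the mean-score outcome. Both are true. Neither corrects the stated power.

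**Conclusion.** The point holds in two parts of different strength.

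- **Firm:** at the plan's own 10% control rate, 397 evaluable participants give about 0.80 power for a 10-point difference, against the stated 0.90. About 532 evaluable would be needed for 0.90. This holds under every standard two-sided formula tried. The cited method paper was not available, and why the figure agrees with 80% power cannot be known from the document.
- **Unsupported, not refuted:** the word conservative. On the stated scale it is justified only for a true control rate below 10% or above 80%, and neither the pilot rate nor the direction meant is given. If the true rate were 20% or 30%, power with 397 would be 0.63 or 0.55; if it were 5%, 0.92. These rates are assumptions, not predictions.

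The figures rest on 1:1 allocation, a two-sided 5% test, a normal approximation for two proportions and no gain from adjusting for education.

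**What to change.** In the Sample size section:

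1. Restate the power of 397 evaluable participants as about 80% at a 10% control pass rate for a 10-point difference.
2. Give the power at other assumed control rates beside it: about 0.92 at 5%, 0.63 at 20% and 0.55 at 30%.
3. Either drop the word conservative, or give the pilot pass rate and say in which direction 10% is cautious. Removing the word alone would leave the wrong power in place.
4. Add that a non-significant pass-rate result will be interpreted from the confidence interval for the difference, which the Analysis section already commits to report.

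Enrolment, conduct and the planned models need not change. The cost is a few sentences, a four-row table and a stated power that is less favourable than the one now printed.

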### Delivery of the interventions

The interventions will be delivered over a period of 7 to 10 weeks to participants in the communities where they live or work. At least 20 research assistants will help in the field recruitment, administration of the intervention, follow-up of participants in the community, and administration of the outcome assessment tool. Each research assistant will be allocated about 25 participants to follow up through the duration of the study. The research assistants will visit all their allocated participants every week, delivering the interventions on portable media players to an average of four participants per day. In this study setting this approach is currently the most practical and most reliable way of delivering the interventions for this trial.

One-time brief interventions have not been shown to improve knowledge of evidence-based medicine principles [35, 36] among health workers. So, as part of our intervention, at every visit we will play a recap of the previous episodes before playing the new episodes. Each participant will receive at least one supervised listening session of every episode, delivered by the research assistants over 7 to 10 weeks. In addition to the messages delivered by the research assistants, we will provide participants with the complete podcast on MP3 players, so that they can replay the episodes at their convenience. For the intervention group we will start with simpler concepts and gradually introduce more difficult concepts as the podcast series progresses, as summarised in Table 5 below. For the control group we will introduce episodes with health conditions that are similar to those being delivered in the intervention group at a defined period of time. The timing of study procedures is summarised in Fig. 2 below.

**Table 5 Tab5:** Sequence of delivery of the episodes of the podcast

Week/Visit	1	2	3	4	5	6	7
Episode	Intro	1 + 2	3 + 4	5 + 6	7 + 8	9	Evaluation^a^

^a^Study evaluation tool (Additional file 3).

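### The stated 90% power for the pass-rate outcome is wrong: 397 analysed participants give about 80% power for 10% v 20%

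*Protocol article*

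**What the plan says.** The Sample size section of the protocol article sets out the calculation for the first primary outcome, the proportion passing. The control rate is given as "Assuming that 10% of the control group will achieve a passing score", and the smallest difference to be detected "in the proportion of respondents with a passing score is 10 percentage points". The error rates are a "power of 0.90, a two-sided" significance level of 0.05. From these the article concludes: "we estimate that 397 participants will be needed to be able to detect an improvement of 10% in the intervention group". It then adds attrition: "Allowing for a 20% loss to follow-up gives us a sample size of 497 participants".

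The section attributes the calculation to a cited odds-ratio method but does not show the formula. It mentions no gain from covariate adjustment and no other allowance that would lower the number. The section on stratification and randomisation specifies equal allocation to the two groups.

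**The concern.** For 10% v 20% at two-sided 0.05, about 400 participants in two arms is the familiar answer for 80% power, not 90%. If the label is wrong, the article credits a primary outcome with a property that the design lacks. A reader of a non-significant pass-rate result would take the chance of having missed the sponsor's own smallest difference of interest as 1 in 10, when it is about 1 in 5.

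**Working it through.** **Inputs, all from the protocol article.** Control pass rate p1 = 0.10 and intervention pass rate p2 = 0.20 (mean 0.15, odds ratio 2.25); two-sided 0.05 (z = 1.960); power 0.90 (z = 1.2816), with 0.80 (z = 0.8416) for comparison; 1:1 allocation; 397 analysed; 20% loss.

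**Is 397 a total or a number per arm?** 397/0.8 = 496.25, rounded up to 497, so the attrition step is correct and 497 is on the same footing as 397. Under Delivery of the interventions there are to be at least 20 research assistants, and "Each research assistant will be allocated about 25 participants to follow up through the duration of the study": 20 × 25 = 500. So 397 is the trial total, about 198.5 per arm. Read per arm instead, it would give 97.8% power, which is not 90% either.

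**Trying to reproduce 397 with the pooled formula.**

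n per arm = [1.960·√(2·0.15·0.85) + z_power·√(0.1·0.9 + 0.2·0.8)]² / 0.10²

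The first term is 1.960 × √0.255 = 0.9897. The second root is √0.25 = 0.5.

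- 80% power: (0.9897 + 0.4208)²/0.01 = 199.0 per arm, total 397.9.
- 90% power: (0.9897 + 0.6408)²/0.01 = 265.9 per arm, total 531.7, i.e. 532.

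The stated figure matches the 80% calculation.

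**Does another formula give 397 at 90%?** The article refers to odds ratios, so two log odds ratio versions are included:

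- separate variances: n per arm = (1.960 + z_power)²·(1/0.09 + 1/0.16)/(ln 2.25)²
- pooled variance: n per arm = (1.960 + z_power)²·2/(0.15·0.85)/(ln 2.25)²

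| Formula (two-sided 0.05) | Total for 90% | Power at 397 |
|---|---|---|
| Log odds ratio, pooled p | 501 | 82.2% |
| Arcsine | 522 | 80.7% |
| Difference, unpooled | 525 | 80.4% |
| Difference, pooled | 532 | 79.9% |
| Log odds ratio, separate variances | 555 | 78.3% |
| Difference, continuity-corrected | 572 | 75.7% |

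The smallest requirement, 501, is 26% above 397 (501/397 = 1.26). Dropping to a one-sided test, which the article does not do, still does not reach 397 at 90%: the lowest total is about 409.

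**Power with the planned numbers.**

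- 397 analysed: z = (0.10·√198.5 − 0.9897)/0.5 = (1.4089 − 0.9897)/0.5 = 0.838, power 79.9%. Exact enumeration of the uncorrected chi-square test with arms of 198 and 199 gives 80.5% to 80.8%, depending on which arm is larger.
- All 497 analysed, no loss: z = (0.10·√248.5 − 0.9897)/0.5 = 1.173, power 88.0%. Exact: 88.4%.
- Difference detectable with 90% power at 397: solving the pooled formula for p2 gives about 21.8%, a difference of 11.8 points.
- Recruitment to keep 90% for 10 points: 532/0.8 = 665.

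**The case against.** The best defence is that the cited odds-ratio method is not reproduced in the article, so the exact formula is unknown, and that 532 is only one formula's answer. The second half stands: the 90% requirement should be read as a range of 501 to 572, and power at 397 as roughly 76% to 82%. The first half does not rescue the claim. Both odds-ratio versions tried fall well short of 90% at 397, and any method that reached it would have to cut the pooled requirement by about a quarter (397/532 = 0.75).

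The planned analysis is logistic regression adjusted for education, which could make actual power somewhat better than these unadjusted formulas show. That is fair, but the sample-size section claims no such gain and gives nothing from which to estimate one.

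The point is also limited in scope. It concerns the pass rate only; the article gives no power for the mean score, the other primary outcome. The error does not bias the estimate or inflate the type I error. The Analysis section promises confidence intervals, which would carry most of the interpretation of a null result, and 80% is a common design level. These points limit the damage but do not make the stated power true.

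**Conclusion.** The concern holds. On the article's own inputs, 397 analysed participants give about 80% power to detect 10% v 20% passing, not 90%. The type II error is about 0.20 against the stated 0.10, and the shortfall for 90% is 532 − 397 = 135 analysed participants by the pooled formula (104 to 175 across the two-sided formulas). The likeliest explanation is that an 80% calculation was labelled 90%; this is an inference, which the article neither confirms nor excludes. The conclusion rests on 397 being a total, equal allocation, an unadjusted comparison, and true rates of exactly 10% and 20%. It applies to the pass-rate outcome only.

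**What to change.** Correct the sample-size paragraph to say that 397 analysed (497 recruited, allowing 20% loss) gives about 80% power to detect 10% v 20% at two-sided 0.05. If useful, add that it gives about 90% power for 10% v 21.8%. Show the formula used, so that the figure can be checked. This costs one sentence and a less favourable power statement; recruitment, randomisation and analysis stay as they are.

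If the sponsor would rather keep 90% for a 10-point difference, the matching target by the pooled formula is 532 analysed and 665 recruited, 168 more than planned. The article describes the trial as still recruiting, so that choice was open when it was written, but restating the power is enough to remove the error.

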### Safety monitoring and adverse events

The National Council of Science and Technology in Uganda has given this study a very low rating for risk to participants. Nonetheless, we will monitor unexpected adverse events and problems that might arise.

### Stakeholder involvement

We have engaged health researchers, journalists, other media and communications practitioners, teachers, and the general public in developing, revising, piloting, and user-testing the podcast [32].

### Reporting, dissemination and notification of results

Authorship of publications arising from this study will be according to contribution. Publications and the resources will be open access, allowing free noncommercial use, distribution, reproduction and further development of the work provided the source is properly cited. We will acknowledge all staff participating in the trial.

The results of this trial will be publicised through a variety of channels. All of the resources will be made available on the IHC project and Testing Treatments interactive websites, and through the Critical Appraisal Resource Library (CARL). They will be disseminated internationally by the IHC project team and through members of our international advisory group, the Cochrane Collaboration (www.cochrane.org), the Evidence-informed Policy Network (www.evipnet.org), the WHO, the Campbell Collaboration (www.campbellcollaboration.org), and other relevant networks and organisations.

